**Outcome measurements**

We will determine if naturopathic medical interventions (*Withania somnifera* extract, daily multi-vitamin, dietary modifications, cognitive-behavioral exercises, relaxation techniques and acupressure massage) reduces the incidence of specific symptoms as measured by the Beck Anxiety Inventory as shown in appendix A. This scale has been independently validated.

**Sample size determination**

Assuming a normal distribution with variances between both populations (pre and post treatment) being essentially equal, we made our power size calculations using Jan deLeeuw's Web-Based Statistics: The Study of Stability in Variation[24]. To obtain a power of 80% with a two sided 5% significance level we would need 54 participants to complete this two-treatment parallel-design study. This will enable the detection of a 40% difference in the Beck Anxiety Inventory rating scale, an amount considered to be clinically significant. Assuming a drop out rate of 30% we will need 78 subjects to commence the trial so that 54 will complete the trial.

**Statistical Analysis**

# Data recovered from the menopause rating scale of each participant will be analysed with the chi-square test and the student’s t-test. Statistical analysis will be conducted on code numbered subjects where treatment protocol is unknown. In other words statistical analysis will be blinded as to the results.

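### The sample size rests on a comparison of normal means, but the analysis section assigns both a chi-square and a t-test to the rating-scale data without saying which one answers the trial's question

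*Protocol*

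**What the plan says.** Sample size determination sets out the model: "Assuming a normal distribution with variances between both populations (pre and post treatment) being essentially equal". From this it concludes: "To obtain a power of 80% with a two sided 5% significance level we would need 54 participants to complete this two-treatment parallel-design study". The effect is given as "detection of a 40% difference in the Beck Anxiety Inventory rating scale". The paragraph does not say what the 40% is a percentage of, prints no SD or reference mean, and names no test.

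Statistical Analysis, the next section, says that data from the menopause rating scale "will be analysed with the chi-square test and the student’s t-test". That instrument has no other place in this trial; the BAI is the scale used in the sample size and under Outcome measurements. The section does not say which test is primary, how a score becomes categories, or what significance level attaches to either test.

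**The concern.** A normal distribution with equal variances is the model for comparing means, so the 80% belongs to a t-test or a close relative. The BAI total runs from 0 to 63. A chi-square test on it needs the total grouped first, which discards information, and the sample-size paragraph makes no allowance for that.

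Three things are at stake. If the chi-square result is taken as the answer, the trial may have well below its stated power. If either test may carry the claim, the false-positive rate is above the stated 5%. If the two tests disagree, the protocol does not say which result counts. Blinded analysis on code numbers does not settle that last point, because the choice can still be made once the codes are broken.

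**Working it through.** **Inputs from Sample size determination:** two-sided 5%, 80% power, 54 completers, 30% dropout.

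**Assumptions, because the protocol is silent:** 1:1 allocation (27 completers per arm), normal scores with a common SD, and one dichotomy of the total score.

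**1. The plan's own figures.** Enrolment: 54 / (1 − 0.30) = 77.1, rounded up to 78, as printed. The 54 itself can be neither reproduced nor refuted without an SD, so the effect has to be solved from it.

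**2. Effect implied by 54 completers.** Find d such that a noncentral t with 52 degrees of freedom and noncentrality d√(27/2) exceeds 2.007 with probability 0.80. This gives d = 0.777. The normal approximation gives (1.960 + 0.842) × √(2/27) = 0.762. If 40% is relative to a reference mean, the implied SD is 0.40 / 0.777 = 51% of that mean.

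**3. Chi-square power at that effect.** For a cut k SD from the control mean, the proportions above the cut are 1 − Φ(k) in the control arm and 1 − Φ(k + 0.777) in the active arm. Power is the sum, over all pairs of binomial counts out of 27 and 27, of the joint probability of each table whose chi-square exceeds 3.841.

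| Cut, SD from control mean | Control above | Active above | Uncorrected | Continuity-corrected |
| --- | --- | --- | --- | --- |
| −2.0 | 97.7% | 88.9% | 21% | 4% |
| −1.5 | 93.3% | 76.5% | 44% | 24% |
| −0.78 (active mean) | 78.1% | 50.0% | 59% | 48% |
| −0.39 (midpoint) | 65.1% | 34.9% | 59% | 48% |
| 0 (control mean) | 50.0% | 21.9% | 59% | 48% |
| +1.0 | 15.9% | 3.8% | 33% | 11% |

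A scan of fixed cuts from −2.5 to +1.6 SD found none above 59% uncorrected, and none more than half a point above 48% corrected. A split at the pooled sample median gives 53% with or without the correction.

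**4. Size needed for 80% at the midpoint cut.** Per arm: [1.960 × √(2 × 0.5 × 0.5) + 0.842 × √(2 × 0.651 × 0.349)]² / (0.651 − 0.349)² ≈ 41.7, so 42 per arm or 84 completers. With d = 0.762 it is 44 per arm, or 88. Either number exceeds the 78 to 80 to be enrolled.

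**5. Type I error if either test may decide.** In 200,000 simulated null trials, with both tests run on the same scores, the chance that at least one rejects at 5% is 7.1%, 8.2% and 9.0% for cuts 0, 0.5 and 1 SD from the common mean, uncorrected. With continuity correction it is 5.1 to 6.3% for cuts out to 1.5 SD. Two independent tests would give 1 − 0.95² = 9.75%. The figures are lower because the tests are correlated.

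**6. The other reading of 40%.** If it meant 40 percentage points of responders, uncorrected chi-square power at 27 per arm would be 84% (70% vs 30%), 87% (60% vs 20%) or 93% (50% vs 10%).

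**The case against.** The strongest reply is that the dichotomised total is not in the protocol. Outcome measurements speaks of the incidence of specific symptoms, and Appendix A scores 21 items in four categories each. Chi-square might therefore be meant for symptom-level data and the t-test for the total. That is possible. It would remove the loss-of-information argument, but it would leave item-level tests that the sample size does not cover either, still unranked against the t-test.

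A second reply is that the choice of primary test and the definition of categories commonly belong in the SAP, which is not shown. Silence on those details would indeed be no finding. Here, however, the protocol itself assigns two tests to the scale data, and one of them does not fit its own sample-size model.

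Three stronger readings are tempting, and the documents support none of them:

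- **That the trial's chi-square power is some fixed figure, such as 44 to 59%.** Those numbers rest on an effect solved from the sample size and on the cut chosen. Other cuts go as low as 21% and below.
- **That 80% power is impossible for chi-square.** Step 6 shows it is reached if 40% means percentage points of responders. That reading sits badly with the normal, equal-variance assumption, but the text does not exclude it.
- **That the plan adds a second confirmatory test at 5%.** Statistical Analysis gives no significance level for either test and no rule that either may win. The type I figures apply only under such a rule, and with continuity correction the excess is small.

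It is also fair that, read literally, the sentence assigns no test to the BAI at all. Correcting the scale name is a separate repair, and doing only that would still leave two unranked tests on the BAI. Likewise, the pre and post treatment wording means that reading the sample size as a two-sample t-test is an inference, though it is the one that fits a parallel design.

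**Conclusion.** The point holds as a mismatch between the sample-size model and the named tests. The protocol sizes the trial for a comparison of normal means, then assigns both a chi-square and a t-test to the scale data without saying which gives the answer.

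The size is conditional on 27 per arm, normal scores, d of about 0.78 and a single dichotomy. On those terms chi-square falls at least 21 points short of the stated 80% at every fixed cut examined (80 − 59 = 21). An either-test rule would put the type I error at roughly 7 to 9% uncorrected, or 5 to 6% corrected. These figures show what the ambiguity could cost; they are not properties of the trial as written. The correction is worth making because it is nearly free and removes a choice that could otherwise be made after the results are seen.

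**What to change.** In Statistical Analysis, name one between-arm comparison of the continuous BAI total at Day 84, from the t-test family, as the sole primary test at two-sided 5%. Restrict chi-square to categorical data, or to a supportive responder table with its categories defined beforehand and no confirmatory claim attached. In Sample size determination, state that the 80% power refers to the continuous comparison only.

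The cost is a few sentences, with no extra participants or data. The one small loss is that a chi-square result alone could no longer support a positive claim.

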**Intervention:** Baseline assessment of both groups will include blood pressure, orthostatic blood pressure, and completion of the Beck Anxiety Inventory (BAI), SF-36, and The Fatigue Questionnaire to determine severity of anxiety symptoms. The active group will receive instruction on stress reduction techniques including diaphragmatic breath control, encouragement to exercise, counselling to identify and eliminate negative stress coping patterns, dietary counselling to ensure proper nutritional content of foods, and reduce reactive hypoglycaemia, Withania somnifera, and a multi vitamin for 12 weeks. The control group will receive instruction on stress reduction techniques including diaphragmatic breath control, encouragement to exercise, counselling to identify and eliminate negative stress coping patterns, and placebo. Every 4 weeks (day 28, day 56) both groups will again have their sitting and orthostatic blood pressure checked, and complete the BAI, SF-36, and The Fatigue Questionnaire. On day 84, a final assessment of sitting and orthostatic blood pressure, BAI, SF-36, and The Fatigue Questionnaire completion will take place.

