### 3.1.5 Patient Selection

80 healthy subjects irrespective of ethnicity, aged 18 to 65 that are self-selected through response to local ads and information talks through Canada Post Centres in Toronto. Contraindications will be ruled out first and informed consent must be received from all participants before eligibility is assigned. Mild anxiety must be exhibited, and a score of 10 must be achieved on the Beck Anxiety Inventory administered on intake in order for patients to qualify.

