## 3.2 Inclusion/Exclusion Criteria

### 3.2.1 Inclusion Criteria

1. Males and females aged 18-65 that are Canada Post employees and members of Canadian Union of Postal Workers (CUPW).

2. Mentally competent subjects able to adhere to the given protocol and treatments administered as interventions.

3. Self-selected candidates identifying themselves to suffer from the symptoms of stress and anxiety for a period of 6 weeks or more and a score of at least 10 on the BAI at the pre-study intake.

4. Normal on physical examination at the pre-study intake, and in the case of abnormalities the medical practitioner considers them to be clinically insignificant.

5. Written and informed consent.

6. The potential candidate must have a family doctor that they have seen in the last 12 months.

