## 3.3 Timeline

1. Labelled as day 0, all potential candidates will be screened for inclusion/exclusion criteria by being asked to read and sign the informed consent, fill in questionnaires including the BAI, be clinically assessed, have their blood pressure taken, and have urine tests to assess for proper liver and kidney function.

1. On day 1, participants that have fulfilled all eligibility criteria and completed the consent form will be randomised into either treatment or control groups using a random number generator by the research assistant who will label the containers of placebo, *Withania somnifera* and multivitamin respectively.
2. Both treatment and placebo groups shall receive the visually identical capsules by the study co-ordinator with instructions on the dosage schedule.
3. Both groups shall take their medications twice daily, one capsule in the morning and one in the evening prior to meals.
4. The treatment shall last 90 days.
5. On day 1, subjects will be clinically assessed, have their blood pressure taken, be interviewed, and complete the SCL-90R, SF-36 and fatique questionnaires. Medication usage will be monitored and compliance to the interventions will be assessed.
6. On day 7, subjects will receive cognitive–behavioral therapy, dietary advice and stress reduction techniques. They will continue these treatment sessions 1 time per week until the completion of the study. (Day 14, 21, 28, 35, 42, 49, 56, 63, 70, 77 and 84)
7. On day 8, subjects in the active group will receive acupressure massage in the treatment of anxiety. They will continue these treatment sessions 1 time per week until the completion of the study. . (Day 15, 22, 30, 38, 45, 52, 60, 68, 75, 82 and 90)
8. On day 28, subjects will be clinically assessed, have their blood pressure taken, be interviewed, and complete the SCL-90R, SF-36 and fatigue questionnaires
9. On day 56, subjects will be clinically assessed, have their blood pressure taken, be interviewed, and complete the SCL-90R, SF-36 and fatigue questionnaires
10. On day 84, subjects will be clinically assessed, have their blood pressure taken, be interviewed, and complete the SCL-90R, SF-36 and fatigue questionnaires

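### The protocol fixes a t-test without baseline adjustment and leaves final versus change score open; adjusting for the intake BAI would gain precision from data already collected

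*Protocol*

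**What the plan says.** **Method.** The protocol's Statistical Analysis section says that the data "will be analysed with the chi-square test and the student’s t-test". No covariate is named there or elsewhere in the document. The section does not say whether the t-test is applied to the Day 84 score or to the change from intake.

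**Instrument.** The subject of that same sentence is "Data recovered from the menopause rating scale of each participant". The Outcome measurements section instead asks whether treatment "reduces the incidence of specific symptoms as measured by the Beck Anxiety Inventory", and Sample size determination is also built on the BAI.

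**Baseline.** Section 3.2.1 requires "a score of at least 10 on the BAI at the pre-study intake", and section 3.1.5 says that "a score of 10 must be achieved on the Beck Anxiety Inventory administered on intake". The abstract (section 2.0) puts the BAI in the baseline assessment of both groups. The Schedule of events table places it on days 0, 28, 56 and 84.

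**Allocation and size.** Under section 3.3, participants are "randomised into either treatment or control groups using a random number generator"; stratification is not mentioned. Sample size determination is set "To obtain a power of 80% with a two sided 5% significance level" and asks for 54 completers, inflated to 78 starters for 30% dropout.

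**The concern.** A two-sample t-test on final scores leaves unused a pre-treatment measurement of the outcome itself. With 27 completers per arm (54 split equally), the standard error of the baseline difference between arms is √(2/27) = 0.27 SD. By chance alone, a baseline gap above 0.3 SD would arise in about 27% of such trials. A final-score t-test allows for this in its standard error but does not correct the estimate.

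A t-test on change does use the baseline, but with a fixed weight of one. That over-corrects when the correlation between baseline and follow-up is modest.

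The protocol does not choose between the two. At stake are some power in a small trial, and a choice between two analyses that could be made after the data are seen.

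**Working it through.** **Inputs from the protocol (Sample size determination).** Two-sided 5% level, 80% power, 54 completers, 30% dropout, a 40% difference in BAI, and equal variances before and after treatment. No SD and no mean BAI are given.

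**Assumptions.** Allocation is 1:1 (the ratio is not stated), so n = 27 per arm. The baseline-to-Day 84 correlation r is not in the documents and is varied from 0.3 to 0.7.

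**1. The plan's own figures.** The inflation reproduces: 54 / (1 − 0.30) = 77.1, or 78 when rounded up to an even number. The 54 cannot be reproduced without an SD, so I back-solve. With 27 per arm, 80% power and t on 52 degrees of freedom, the detectable difference is d = 0.777 SD (0.762 with the normal approximation). If the 40% is relative to the mean BAI, this implies an SD of 0.40 / 0.777 = 0.51 of that mean.

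**2. Variance of each analysis, relative to a final-score t-test.**
- Final-score t-test: 1.
- Change-score t-test: 2(1 − r), given equal variances at both times.
- ANCOVA: 1 − r², times a chance-imbalance factor of 1 + 1/50 = 1.02, with 51 degrees of freedom.

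**3. Effective standardised difference,** 0.777 divided by the square root of that variance:

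| r | Final score | Change score | ANCOVA |
|---|---|---|---|
| 0.3 | 0.777 | 0.777/√1.4 = 0.657 | 0.777/√(0.91 × 1.02) = 0.806 |
| 0.5 | 0.777 | 0.777/√1.0 = 0.777 | 0.777/√(0.75 × 1.02) = 0.888 |
| 0.7 | 0.777 | 0.777/√0.6 = 1.003 | 0.777/√(0.51 × 1.02) = 1.077 |

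**4. Power,** from the non-central t distribution with non-centrality equal to the effective difference × √(27/2):

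| r | t-test, final | t-test, change | ANCOVA |
|---|---|---|---|
| 0.3 | 80% | 66% | 83% |
| 0.5 | 80% | 80% | 89% |
| 0.7 | 80% | 95% | 97% |

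ANCOVA is ahead of both t-tests in every row. The size of the gain depends on which t-test is meant. Before the 1.02 factor, ANCOVA's variance is 91%, 75% and 51% of the final-score test's. It is (1 + r)/2 = 65%, 75% and 85% of the change-score test's. At r = 0.5 the two comparisons coincide, and the gain is worth 54/0.75 = 72 completers instead of 54.

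**5. Cost if baseline predicts little.** ANCOVA power is 79.2% at r = 0, 79.6% at r = 0.1 and 80.8% at r = 0.2. Break-even against the final-score t-test therefore lies between 0.1 and 0.2, and the most that can be lost is 0.8 of a point.

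**The case against.** **The t-test may already use the baseline.** A reader might infer that the stated test ignores the intake BAI. The documents do not support that. The Statistical Analysis section is silent on the score, and section 4.0 speaks of whether any change differs from control, which makes a change-score t-test a natural reading. This stands, which is why both readings are computed. On the change reading at r = 0.7, the gain is only from 95% to 97%.

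**An unadjusted t-test is valid.** This also stands. Chance imbalance is in its standard error, and the type I error is controlled. A reader might infer bias; there is none.

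**Adjustment is often left to a SAP.** That is true, and one may exist. But the protocol does not leave the method open: it names the test. The point concerns what it fixes, not an omission.

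**The sentence is not about the BAI.** Literally it concerns another instrument. Applying it to the BAI rests on the Outcome measurements and Sample size determination sections. The wrong instrument is a separate and more serious error, and it means that the sentence must be rewritten in any case.

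**The gain is easily overstated.** A reader might take adjustment to be free, or to be the largest precision gain available. Neither holds. It costs a degree of freedom, and nothing here compares it with, for example, using the Day 28 and Day 56 BAI or losing fewer than 30% of participants. The size rests on an assumed r, and the entry cut-off of 10 truncates baseline scores and may lower it.

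**Conclusion.** The point holds as one of efficiency and of an unsettled choice of score. At 27 completers per arm and 0.78 SD, ANCOVA adds about 3, 9 and 17 points of power over a final-score t-test for r = 0.3, 0.5 and 0.7. Over a change-score t-test it adds about 17, 9 and 2 points. The direction is the same under either reading across that range.

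The sizes depend on 1:1 allocation, an effect size back-solved from a 54 that cannot be checked, an assumed correlation, and the protocol's own assumption of equal variances before and after treatment. This is an improvement worth making in a sentence that has to be corrected anyway. It does not show the planned test to be invalid.

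**What to change.** Rewrite the Statistical Analysis section to name the BAI total at Day 84 as the outcome. Compare arms by ANCOVA with intake BAI as covariate, and report the adjusted difference with its 95% confidence interval. This also settles final versus change score before any data are seen.

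Treat the SF-36 and fatigue scores in the same way, each with its own baseline. First reconcile the fatigue instrument: the abstract describes 11 items, while Appendix C contains 20 statements.

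The cost is a sentence or two of text and one degree of freedom. No new data, visits or participants are needed.

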# 2.0 Scientific abstract

**Background:** Anxiety disorders are among the most prevalent psychiatric disorders in the Canada Post workers general population, yet there is a lack of information with regards to safety and efficacy of combined naturopathic approache for anxiety. There is a body of literature that supports usage of some herbs, dietary advice, exercise, and cognitive techniques in the treatment of anxiety, however there is very little research on the combined approach in a workplace setting. We aim to evaluate the efficacy and safety of dietary advice, exercise, cognitive counselling, Withania sominfera and a Adult Multi One multivitamin on common indicators of anxiety

**Design:** Phase II Randomised parallel clinical trial.

**Objective:** To determine if dietary modification, exercise, counselling, Withania somnifera, and a multi vitamin decreases the anxiety scores in a working population at Canada Post.

**Null hypothesis:** Dietary modification, exercise, counselling, Withania somnifera, and a multi vitamin has no effect on anxiety scores.

**Participants:** 80 Canada Post employees who are who are experiencing the symptoms anxiety (who score over 10 points on the Beck Anxiety Inventory) will be randomised to two groups: one receiving dietary modification, exercise, counselling, Withania somnifera, and a multi vitamin (active group), and one receiving dietary modification, exercise, counselling, and placebo (control group).

**Setting:** Clinical trial will be conducted at the Canada Post Gateway Processing Plant.

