On subsequent visits, both the control and intervention group patients will receive treatments including cognitive behavioural stress reduction, behavioral psychotherapy, examination of sleep patterns and treatment for any insomnia. Both groups will be encouraged to engage in an active exercise routine. The active group will also receive daily good quality multi vitamin (Ultra Balance III by Douglas Labs) and *Withania somnifera* (300 mg standardized to 1.5% Withanolides, bid) (Ashwagandha by Douglas Labs). The control group will receive placebo identical in look and frequency of dosage to the treatment group. On subsequent visits, the active group will receive lifestyle and diet counseling, and will continue with behavioral psychotherapy. Active group patients will also receive acupressure massage for at least 15 minutes once per week.

Both the active and control arm will attend weekly 30 minute treatments, for a total of 12 treatments over 12 weeks. Both groups will complete the Beck Anxiety Inventory, S-90-R, SF-36, Fatigue Questionnaire, and the Perceived Benefit of Treatment questionnaires at 4, 8, and 12 weeks. At these times, the sitting and orthostatic blood pressures will also be recorded. Both groups will also hand in the Pain Diet, Absenteeism, Pain Medication and Therapies Diary every week.

Study period is 12 weeks. Clinical evaluations will be performed at:

- Baseline (Visit 1 - Day 1)
- Interim for the treatment groups: (Visit 2 - Day 7, Visit 3- Day 14, Visit 4 – Day 21, Visit 4 – Day 28, Visit 5 – Day 35, Visit 6 – Day 42, Visit 7 – Day 49, Visit 8 – Day 56, Visit 9 – Day 63, Visit 10 – Day 70, Visit 11 – Day 77)
- Interim for the control groups: (Visit 2 - Day 7, Visit 3- Day 14, Visit 4 – Day 21, Visit 4 – Day 28, Visit 5 – Day 35, Visit 6 – Day 42, Visit 7 – Day 49, Visit 8 – Day 56, Visit 9 – Day 63, Visit 10 – Day 70, Visit 11 – Day 77)
- End of Treatment (Visit 12 - Day 84), Questionnaires and Medication diaries filled in for the last time

Follow-up data will be collected at 2, 6, and 12 months post treatment via a mailed questionnaire package containing the Beck Anxiety Inventory, S-90-R, SF-36, Fatigue Questionnaire, and the Perceived Benefit of Treatment questionnaires, as well as the Diet, Absenteeism, Medication and Therapies Diary. Non-responders will receive reminders by post. If this is unsuccessful, the patients will be telephoned.

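### The tests the protocol names cannot use the interim BAI scores of participants who leave, in a trial that plans for 30% dropout

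*Protocol*

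**What the plan says.** The Statistical Analysis section states that each participant's data will be "analysed with the chi-square test and the student’s t-test". It names no other test or model. It gives no time point, analysis set or rule for missing values. It also names the menopause rating scale as the instrument. The Outcome measurements section makes the BAI the outcome, so I read the sentence as referring to the BAI; the wrong instrument name is a separate error.

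The Sample size determination section says "we would need 54 participants to complete this two-treatment parallel-design study", and then "Assuming a drop out rate of 30% we will need 78 subjects to commence the trial so that 54 will complete the trial".

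On visits, the Methodology section says "Both groups will complete the Beck Anxiety Inventory, S-90-R, SF-36, Fatigue Questionnaire, and the Perceived Benefit of Treatment questionnaires at 4, 8, and 12 weeks". The Intervention paragraph of the abstract (section 2.0) and the schedule-of-events table agree that the BAI is taken at Days 28, 56 and 84. The section 3.3 timeline lists other questionnaires on those days but omits the BAI, and should be reconciled with the rest.

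**The concern.** A two-sample t-test takes one value per participant. Applied to the Day 84 BAI, or to change from intake to Day 84, it has nothing to use for a person who left earlier. That person's Day 28 and Day 56 scores cannot inform the Day 84 comparison. Separate t-tests at each visit would use the interim scores at those visits, but not at Day 84.

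The harm comes if leaving depends on how the participant is doing, and does so differently by arm. Those who remain are then no longer comparable. The protocol makes this plausible, though not certain:
- The design is single blinded (section 3.1.4), and only the active group receives weekly acupressure, so the treatment packages visibly differ although the capsules match.
- The Safety part of section 1.0 withdraws participants whose health is judged compromised, which may be related to outcome.
- Section 4.0 itself names loss of participation as a threat to the results if the trial ran longer.

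**Working it through.** **1. The plan's own figures.** Inputs from Sample size determination: 54 completers, 30% dropout, 80% power, two-sided 5%.
- 54 / (1 − 0.30) = 77.14, rounded up to 78. This reproduces the stated figure.
- Planned loss: 78 − 54 = 24, and 24/78 = 31%.
- The 54 itself cannot be reproduced. The effect is given only as "This will enable the detection of a 40% difference in the Beck Anxiety Inventory rating scale", with no control mean and no standard deviation.
- Assuming 1:1 allocation (no ratio is stated), 27 per arm gives a detectable difference of (1.960 + 0.842)/√(27/2) = 0.76 SD by the normal formula, or 0.777 SD by the noncentral t. I use 0.777 SD as the true effect below.
- If all 78 gave a Day 84 value, power at that difference would be about 92%.

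**2. Simulation under assumed dropout patterns.** The documents give none of these inputs; all are assumptions.
- 39 per arm; normal scores with SD 1 at intake and Days 28, 56 and 84; equal correlation of 0.5 or 0.7 between visits; effect at visit j equal to 0.777 × j/3; 1,500 runs per setting.
- After Day 28 and again after Day 56, leaving has log-odds log(0.163/0.837) + s × latest score. With s = 0 the total loss is 1 − (1 − 0.163)² = 30%. With s = ±1 the odds ratio is e¹ = 2.7 per SD.
- The all-visit estimate is the likelihood estimate for monotone dropout, from sequential regressions on arm and all earlier scores.

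Each range covers the two correlations. Effects are SD units in favour of active.

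| Who leaves | Loss | Day 84 t-test estimate | t-test power | All-visit estimate | t-test type I error, no true effect |
|---|---|---|---|---|---|
| Unrelated to score | 30% | 0.78–0.79 | 80–82% | 0.77–0.78 | 5% |
| High scorers, both arms alike | 31% | 0.71–0.74 | 76–77% | 0.77 | 3–6% |
| High scorers, control arm only | 33% | 0.56–0.62 | 53–62% | 0.78–0.79 | 8–12% |
| High scorers in control, low scorers in active | 39–40% | 0.27–0.42 | 17–30% | 0.79 | 23–37% |

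Loss is for the runs with a true effect. In the last row it exceeds the planned 30%, so that row is an extreme.

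**3. A second set with loss held at 30%.** 80 randomised; 10% lost before Day 28 and about 20% after at least one interim BAI; same correlations; 4,000 runs per setting; leaving in opposite directions by arm.
- Odds ratio 2.7 per SD: t-test 0.51–0.58 SD, power 48–58%; t-test with baseline adjustment 0.68–0.70 SD; all-visit analysis 0.78–0.79 SD. With no true effect, t-test type I error is 12–19%.
- Odds ratio 1.6 per SD: t-test 0.62–0.67 SD.

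**4. Reading the two together.** Across the arm-dependent patterns the t-test estimate runs from 0.27 to 0.67 SD, that is 1 − 0.67/0.78 = 14% to 1 − 0.27/0.78 = 65% too small. In these patterns the bias works against the active arm. With no true effect, swapping the arms reverses its sign, so it could equally favour active treatment.

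**5. Precision when leaving is unrelated to score.** The standard error falls from 0.27–0.28 with the t-test to 0.19–0.24 with the all-visit analysis. Most of that gain comes from intake BAI: compared with a baseline-adjusted analysis of those measured at Day 84, the all-visit variance is only about 2–5% lower.

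**The case against.** A reader might infer that the protocol prescribes a completers-only analysis and throws interim scores away. It says neither. The Statistical Analysis section refers to each participant and fixes no visit. Inflating a sample size for dropout is routine and does not define an analysis set. An SAP that is not shown may define the set and the handling of missing values, so their absence is no finding. This part of the objection stands. What remains is that the protocol positively names simple two-group tests, and those fit a design with planned 30% loss and two interim BAI visits badly.

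A reader might also infer that the result will be biased by a known amount. The documents do not support that. Dropout mechanism, timing, SD and correlation are all assumed, and the same opposite-direction pattern gave 0.27–0.42 SD in one set of simulations and 0.51–0.58 SD in the other. With random loss there is no bias. With loss driven alike in both arms it is small. Baseline adjustment alone recovers much of the rest.

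Third, the remedy has limits. Only dropout depending on observed scores was simulated, which favours the likelihood model. The rejection rate of that model was not simulated, only the mean and spread of its estimate. A model with intake BAI solely as a covariate would gain nothing from people lost before Day 28, and a Day 84 t-test does not probe departures from missing at random. These points stand and shape the fix.

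**Conclusion.** The point holds in a limited form. The only tests named take one value per person, the trial expects to lose 24 of 78 participants, and the BAI is scheduled at two interim visits. A Day 84 t-test without imputation therefore cannot use what is known about those who leave.

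Whether this biases the result depends on why people leave, which the documents do not say. Bias and inflated type I error arise when leaving depends on observed BAI differently by arm. The illustrative range is 0.3 to 0.67 SD for a true 0.78 SD. It rests on 1:1 allocation, normal scores, visit correlations of 0.5 to 0.7, and odds ratios of 1.6 to 2.7 per SD. The all-visit analysis stayed at 0.77–0.79 SD in every pattern, but only because leaving was made to depend on observed scores. The change is worth making because it is cheap and the planned loss is large, not because bias has been shown.

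**What to change.** - **Main analysis.** Replace the t-test as the main BAI analysis with a repeated-measures likelihood model on all BAI visits: arm, visit, arm-by-visit, unstructured covariance. Enter intake BAI as a baseline response constrained equal across arms, so that everyone randomised contributes, including those lost before Day 28. Analyse all as randomised and take the Day 84 arm contrast as the result. The model has 1 + 2 × 3 = 7 means and 4 × 5/2 = 10 covariance parameters.
- **Supportive analysis.** Keep the Day 84 t-test.
- **Sensitivity.** Add one analysis for departures from missing at random, for example a delta adjustment to the Day 84 values of those who left.
- **Consistency.** Name the BAI in the Statistical Analysis section, and reconcile the section 3.3 timeline with the visits at which the abstract, the Methodology section and the schedule table place the BAI.

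The cost is a change of wording and a slightly more complex model. No extra visits, data or participants are needed.
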